### Expected Primary Outcomes

#### Dietary Intake: Quantity and Quality

Change in dietary intake between baseline and four subsequent follow-up visits 6 weeks apart will be assessed through a questionnaire. Based on consumption recorded in the food diary, data will be collected on the frequency and amount of all kinds of food consumed at each meal, including fruits and vegetables, red meat, white meat, legumes, nuts, eggs, dairy products, added table salt, and drinks (eg, carbonated drinks, fresh juices, and prepared juices). Averages will be calculated to determine the daily intake. Food sizes and amounts will be explained with the help of model utensils (ie, plate, bowl, and glass).

Dietary risk scores, ranging from 0 to 18, will be calculated based on the consumption of food items from six main food groups. Based on portions and diet quality, the score for each food group will be 0, 1.5, or 3 (Table 1) [58]. The total score will be the sum of individual food group scores. The higher the aggregate score, the poorer the dietary quantity and quality, and vice versa. Hence, a score of 18 indicates a highly inadequate dietary intake, a score of 9 indicates a nearly adequate dietary intake, and a score of 0 indicates an adequate diet [58].

**Table 1 table1:** Dietary risk score for six food groups.

Food group and characteristics^a^		Dietary risk score		
		0	1.5	3

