### Counseling for Diet, Supplement Use, and Physical Activity

#### Diet

Women randomized to the intervention group will receive dietary advice based on the World Health Organization (WHO) guidelines for healthy eating during pregnancy and breastfeeding [47]. We have also consulted guidelines by the WHO for healthy diet [51], the ACOG for nutrition during pregnancy [52], and the Food and Agriculture Organization of the United Nations [53] for the development of content for the push messages. In these messages, consumption of food from six main food groups will be encouraged as follows: bread, cereals, rice, and potato group (6-11 portions per day); vegetable group (at least 3 portions per day); fruit group (at least 2 portions per day); milk and dairy products group (3 portions per day); fish, poultry, meat, and beans group (2 portions per day); and butter, margarine, and oil group (less than 30% of total calories, preferably as unsaturated fats) [51]. In addition, women will be advised to consume three meals and two snacks per day to avoid prolonged periods of fasting and to consume monounsaturated fats, adequate protein, fiber-rich carbohydrates, and at least two servings of omega-3–rich fish per week. Consumption of vitamin A will be encouraged from plant sources as beta carotene. Further, advice will be given to limit intake of carbohydrates with a high glycemic index (eg, fruit juices and sodas).

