**Fish, poultry, meat, and beans**				
	Quantity	2 portions	1 portion	<1 portion
	Quality	All sources (fish and meat 2 times/week; plant-based protein ≥4 times/week)	Fish >2 or <1 times/week; meat >2 or <1 times/week; plant-based protein 2 to <4 times/week	No fish, no plant-based protein, only meat

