**Oils and fats**				
	Quantity	25% to 30% of total calories	30% to 35% of total calories	>35% of total calories
	Quality	Polyunsaturated	Monounsaturated	Saturated

^a^The quantity and quality refer to the daily consumption.

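### The dietary risk score, a primary outcome, conflicts with the intervention's own dietary advice, leaves ordinary intakes without a score, and has no stated rule for combining its quantity and quality rows

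*Protocol article*

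**What the plan says.** The Abstract lists change in mean dietary risk score from baseline to each follow-up among the primary outcomes. The section Dietary Intake: Quantity and Quality defines it: "Dietary risk scores, ranging from 0 to 18, will be calculated based on the consumption of food items from six main food groups". Within a group, "Based on portions and diet quality, the score for each food group will be 0, 1.5, or 3", and "The total score will be the sum of individual food group scores". On direction: "The higher the aggregate score, the poorer the dietary quantity and quality, and vice versa". A total of 0 denotes an adequate diet. On the intake to be scored: "Averages will be calculated to determine the daily intake". Table 1 then gives every food group a quantity row and a quality row, each with its own 0, 1.5 and 3 cells.

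The Diet subsection of the counselling section sets out the advice for the intervention group. It includes 6–11 portions a day of bread, cereals, rice and potato, and fats below 30% of calories, preferably unsaturated. Women are also advised to "consume monounsaturated fats, adequate protein, fiber-rich carbohydrates, and at least two servings of" omega-3-rich fish a week.

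In Table 1, the 1.5 quality cell for the fish, poultry, meat and beans group begins "Fish >2 or <1 times/week". Monounsaturated fat is the 1.5 quality cell for oils and fats. The 0 cell for fat quantity is "25% to 30% of total calories".

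**The concern.** An outcome that measures response to dietary advice should not give a worse category to an intake that the advice recommends, and every intake that can occur should map to exactly one score. As printed, Table 1 fails on both counts.

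Some women who follow the intervention's advice cannot obtain the best quality score in two food groups. Other women, including most of those in the advised cereal range, have no quantity score. Both the between-group comparison of the score and the planned mixed model of the fraction scoring adequately (Statistical Analysis) would then rest on decisions that the plan does not state.

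**Working it through.** **1. The stated range.** There are six groups, one score per group, and a maximum of 3 per group: 6 × 3 = 18, with minimum 0. The 0–18 range is reproduced.

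**2. Combining the two rows.** Each group has 3 × 3 = 9 quantity-by-quality combinations. The rows agree in 3 and disagree in 6. The article gives no rule for the disagreements. Four candidate rules give:

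| Rule | Possible group values | Total range | Combinations outside 0/1.5/3 |
|---|---|---|---|
| Sum | 0, 1.5, 3, 4.5, 6 | 0–36 | 3 of 9 |
| Mean | 0, 0.75, 1.5, 2.25, 3 | 0–18 | 4 of 9 |
| Worse of the two | 0, 1.5, 3 | 0–18 | 0 of 9 |
| Better of the two | 0, 1.5, 3 | 0–18 | 0 of 9 |

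So at least two rules satisfy both stated constraints, and they give different scores whenever the rows disagree.

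**3. Advice against score.**
- Fish: three servings a week meets the advice of at least two, but falls in the 1.5 quality cell. Exactly two can score 0.
- Fat type: monounsaturated fat is advised but scores 1.5. The 0 cell is polyunsaturated.
- Cereals: 6–11 portions are advised, but the 0 cell is 6 portions and nothing lies above it. The score is missing, not worse.
- Fat quantity: below 30% of calories is advised, but below 25% has no cell. Again the score is missing, not worse.

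Take one woman who eats fish three times a week and uses monounsaturated fat, has quantity 0 in both of those groups, and scores 0 everywhere else. Each of the two groups has the pair (0, 1.5). Her total is 2 × 1.5 = 3 under the sum or worse-of rule, 2 × 0.75 = 1.5 under the mean, and 0 under better-of. Whether she counts as fully adequate depends on the unstated rule. This illustrates one woman, not a shift in an arm mean.

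**4. Coverage of the quantity rows.** Assume whole portions are counted over a 7-day record, so daily averages move in steps of 1/7. Applying the cells as printed:

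| Group (range checked, portions/day) | Possible averages | Without a cell | Where |
|---|---|---|---|
| Cereals, advised range 6–11 | 36 | 35 | above 6 |
| Fruit, 0–4 | 29 | 6 | between 1 and 2 |
| Fish, poultry, meat, beans, 0–4 | 29 | 20 | between 1 and 2 (6), above 2 (14) |
| Dairy, 0–5 | 36 | 14 | above 3 |
| Vegetables, 0–5 | 36 | 0 | none |

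These count possible values, not women. No intake distribution is given.

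**5. Quality gaps and overlaps.** Fish from 1 to below 2 times a week has no cell. Neither does fruit that is mostly but not only whole. Fat at exactly 30% of calories sits in both the 0 and 1.5 quantity cells. All-raw vegetables satisfy both the 0 cell (more than a third raw) and the 3 cell (one form only).

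**The case against.** The strongest reply is that much of this is table shorthand. A top cell of 6, 2 or 3 portions may mean at least that many, and 1 portion of fruit may mean 1 to below 2. The combining rule may stand in the full protocol or in the cited scoring source. This has force for several quantity gaps and for the combining rule, which is therefore the weaker part of the point. But Table 1 does use a greater-or-equal sign for fruit and vegetables and not for the other groups. No such reading removes the fish and monounsaturated-fat conflicts, which lie between two places in the same article. Nor does it supply cells for fat below 25% of calories, fish 1 to below 2 times a week, or mostly-whole fruit.

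A reader might also infer more than the documents support:

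- **That Table 1 cannot produce 0–18.** It can, because the text gives one score per group. The 0–36 range arises only if both rows are added, which the text does not direct.
- **That success in these items always worsens the score.** Moving from saturated to monounsaturated fat improves the fat-quality row from 3 to 1.5, and moving from under one fish serving a week to exactly two can improve the fish row. Worsening needs a woman who starts in the best cell and leaves it; for others the effect is a cap.
- **That only the intervention arm is affected.** The push messages go only to that arm, but Study Design says controls receive counselling of similar content, and their brochure is not shown.
- **That unblinded staff will code gaps by hand.** No passage says so, and the app is described as generating dietary risk scores.
- **That a 1.5-point step can be set against the difference detectable with 107 women per arm.** That would compare one woman's step with a difference in arm means. The 107 was derived for a physical-activity proportion, and no SD for this score is given.

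**Conclusion.** The point holds on the printed text. Two advised intakes fall in a worse quality category than the best one, several advised or ordinary intakes have no category, some fall in two, and the step from two rows to one group score is not stated. A primary outcome is therefore not uniquely determined as the article defines it, and this should be settled before analysis.

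The size and direction of the net effect on the arm difference cannot be computed. That would need the intake distributions, the content of the control brochure and the combining rule, and the article gives none of these. The coverage counts rest on whole portions over seven days and on reading the cells literally. If the top cells mean at least, the cereal, dairy and upper fish/meat/beans quantity gaps close; the fish and fat-type conflicts and the remaining gaps do not.

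**What to change.** Before analysis, and without reference to outcome by arm, the investigators should:

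1. Reconcile the Diet counselling text with Table 1 item by item. Which threshold prevails is for them to decide and justify. Neither the advice nor the table should be presumed to give way.
2. Make the cells of each row contiguous, non-overlapping and exhaustive on the averaged scale.
3. State one rule that turns the quantity and quality rows into a single 0, 1.5 or 3 per food group, so that the 0–18 range follows from it.
4. Freeze the algorithm, date it, and apply it with one script to the recorded portions of both arms at every visit, including those already completed.

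The cost is modest. Recruitment was complete, but the Results section places analysis in 2023, with 170 of the 234 women remaining in the study having finished all four follow-ups. Portions and food quality are recorded, so completed visits can be rescored, provided the stored detail is fine enough for the revised cells. The downsides are some rescoring work and less direct comparability with the cited scoring source. Because the trial is unblinded and partly complete, the record should show that the changes were made without sight of results by arm.

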**Bread, cereals, rice, and potato**				
	Quantity	6 portions	3 to <6 portions	<3 portions
	Quality	≥50% of whole grains	25% to <50% of whole grains	<25% of whole grains
**Fruits**				
	Quantity	≥2 portions	1 portion	<1 portion
	Quality	Whole fruit consumption	<50% of whole fruits and >50% shakes or fruit juices	Juices and/or shakes only
**Vegetables**				
	Quantity	≥3 portions	1.5 to <3 portions	<1.5 portions
	Quality	>1/3 raw and <2/3 cooked	<1/3 raw and >2/3 cooked	Only in one form
**Fish, poultry, meat, and beans**				
	Quantity	2 portions	1 portion	<1 portion
	Quality	All sources (fish and meat 2 times/week; plant-based protein ≥4 times/week)	Fish >2 or <1 times/week; meat >2 or <1 times/week; plant-based protein 2 to <4 times/week	No fish, no plant-based protein, only meat
**Milk and dairy products**				
	Quantity	3 portions	1.5 to <3 portions	<1.5 portions
	Quality	Milk and dairy products	Milk or dairy products	None
**Oils and fats**				
	Quantity	25% to 30% of total calories	30% to 35% of total calories	>35% of total calories
	Quality	Polyunsaturated	Monounsaturated	Saturated

^a^The quantity and quality refer to the daily consumption.

#### Supplement Use

Supplement use will be assessed by recording the frequency of consumption of folic acid, iron, calcium, and vitamin D in the questionnaire. The frequency will be categorized as daily (7 days per week), often (4-6 days per week), and sometimes (1-3 days per week). Also, a total score ranging from 0 to 12 will be assigned, where use of each supplement will be scored 0 for daily use, 1.5 for less than daily use, and 3 for no consumption (Table 2). The total score will be the sum of each supplement use score and will be monitored at each follow-up.

**Table 2 table2:** Scoring for use of each supplement.

Micronutrient supplement	Frequency of use by score		
	Adequate (0)	In between adequate and inadequate (1.5)	Inadequate (3)
Calcium (1.5-2 g)	Daily	Often or sometimes	Not consumed
Folic acid (0.4 mg)	Daily	Often or sometimes	Not consumed
Iron (30-60 mg)	Daily	Often or sometimes	Not consumed
Vitamin D (200 IU)	Daily	Often or sometimes	Not consumed

#### Physical Activity

Intensity and duration (minutes) of physical activity will be assessed through the questionnaire at baseline and at each follow-up. Walking slowly and household tasks, such as cooking, ironing, light physical work, driving, and washing dishes, will be categorized as mild-intensity activities [59]. Brisk walking; gardening; household chores, such as sweeping, washing, vacuuming, and mopping; actively playing with children; and carrying loads under 20 kg will be classified as moderate-intensity activities [60,61]. On the other hand, vigorous-intensity activities will include running, fast cycling, aerobics, swimming, sports games, or carrying loads over 20 kg [60,61].

### Expected Secondary Outcomes

#### Maternal Health

The following four maternal conditions will be identified through the medical records.

Pre-eclampsia will be defined as new onset of hypertension after 20 weeks of gestation along with proteinuria (ie, a spot urine protein to creatinine ratio of ≥30 mg/mmol) and/or evidence of maternal acute kidney injury, liver dysfunction, neurological features, hemolysis or thrombocytopenia, and/or fetal growth restriction [62].

Gestational hypertension will be defined as new onset of hypertension (ie, blood pressure of ≥140 mm Hg systolic or ≥90 mm Hg diastolic at or after 20 weeks’ gestation) [62].

Gestational diabetes will be defined as diagnosis made by a single-step 75-g oral glucose tolerance test conducted between 24 and 28 weeks of gestation or at any other time, with one or more of the following results: (1) fasting plasma glucose of 5.1 to 6.9 mmol/L (92-125 mg/dL), (2) 1-hour post–75-g oral glucose load of ≥10 mmol/L (180 mg/dL), and (3) 2-hour post–75-g oral glucose load of 8.5 to 11.0 mmol/L (153-199 mg/dL) [63].

Due to the expected low incidence of these conditions and given our small sample size, we shall pool these conditions as adverse maternal outcomes.

Gestational weight gain will be determined from weights recorded during the first, second, and third trimesters. Centiles and *z* scores will be assessed using the international gestational weight gain calculator based on the INTERGROWTH-21st (International Fetal and Newborn Growth Consortium for the 21st Century) Project standards for gestational weight gain [64,65].

#### Newborn Health

At birth, weight, height, and gestational age will be determined from medical records. Birth weight (in grams) will be the first weight of an infant measured soon after birth, ideally within the first hours before significant postnatal weight loss has occurred [66]. Length at birth will be measured from head to toe (in cm). Both weight and length will be adjusted for sex and gestational age at birth and compared with the INTERGROWTH-21st Project reference [67]. Preterm birth will be defined as spontaneous birth before completion of 37 weeks of gestation [68].

#### Infant Health

BMI will be assessed by measuring the weight and length of the infant at their first birthday using standardized equipment (seca 417 length scale and LAICA weight scale, model No. PS3001W1). BMI will be compared with the sex- and age-adjusted INTERGROWTH-21st reference [67]. At the same visit, resting blood pressure will be assessed using the Dinamap VS-900 vital signs monitor (Mindray), with an appropriate infant-sized cuff while the infant is in a state of calm. Two readings will be taken from the left arm, and an average will be calculated [69]. Mean systolic and diastolic blood pressure that is more than the height- and gender-based 90th centile will be considered high risk [70].

#### mHealth Outcomes

Compliance with the intervention will be defined by the percentage of participants who complete the 6-month program [36]. Usability of the mHealth program will be assessed through a usability questionnaire, where items are rated on a 5-point Likert scale with the following responses: 1 (always), 2 (often), 3 (sometimes), 4 (rarely), and 5 (never), or 1 (strongly agree), 2 (agree), 3 (neutral), 4 (disagree), and 5 (strongly disagree).

### Type of Analysis

The data for the study participants will be analyzed based on the group to which they were initially assigned, irrespective of the intervention they received using the intention-to-treat approach [71]. This will preserve the benefits of randomization and will allow us to draw inferences regarding the efficacy of the intervention [71].

### Statistical Analysis

Data will be entered and analyzed using Stata software (version 12; StataCorp LP). Data from the intervention group will be digitalized and uploaded to the app. Categorical variables will be reported as frequencies and percentages. Continuous variables will be reported as means and SDs or medians and IQRs, as appropriate. General characteristics, nutritional change in the form of dietary risk score, supplement use, maternal outcomes, gestational weight gain, birth weight and length, BMI, and blood pressure will be compared using chi-square tests for proportions and *t* tests and Mann-Whitney *U* tests for continuous variables. A mixed-model method will be used to take into account the repeated measurements and correlation while modeling the fraction that scores adequately at each of the follow-up time points. In order to minimize selection bias, we will use multiple imputation models to handle missing data from participants who prematurely leave the study. Possible confounding variables, such as age, BMI, parity, previous history of miscarriage, socioeconomic status, educational status of the women, and occupation, will be assessed and adjusted. Moreover, interactions will be reported if present in the model.

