### Study Design

This study is a parallel-group, randomized controlled superiority trial with two groups (ie, intervention and control) having an allocation ratio of 1:1. The trial was registered at ClinicalTrials.gov (NCT04216446) on January 2, 2020. The intervention to be tested is an mHealth program that was developed locally to collect dietary, supplement use, and physical activity information from pregnant women and to provide personalized counseling tailored to the screening information. The control group will receive standard counseling with similar content, but the content will not be personalized and will be delivered through face-to-face sessions.

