### Sampling Strategy and Randomization

Participants were identified using a purposive sampling strategy and were randomly assigned to the study groups using simple block randomization (block size of 6). The Clinical Trials Unit at AKUH facilitated the computer-generated randomization and provided opaque, sealed envelopes to the research team to ensure concealment of the assignment (Figure 1).

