## Results

The screening questionnaire was pretested in 2020 on 15 pregnant women (5% of the sample). We completed the study recruitment in September 2021. Of the 300 recruited participants, 22.0% (n=66) were lost to follow-up due to miscarriage, change of hospital, refusal by family to continue, or migration to another part of the country. Of these 66 participants, 64% (n=42) belonged to the intervention group. Of the 234 participants who remained in the study, 72.6% (n=170) have completed their four follow-up sessions. The maternal and newborn outcomes have been assessed for 64.1% (n=150) of the participants, and the infant assessment has been conducted for 2.6% (n=6) of the participants. We plan to complete all follow-ups and outcome assessments by March 2023 and analysis by June 2023. Results are expected to be published by the end of 2023. Trial results will be disseminated through publications and conference proceedings.

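### The multiple-imputation rule does not separate pregnancy loss from withdrawal, so as written it reaches women for whom later outcomes are undefined; unequal loss by arm leaves the comparison resting on an untested assumption

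*Protocol article*

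**What the plan says.** All references are to the protocol article.

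- **Statistical Analysis** gives one rule for incomplete data: "we will use multiple imputation models to handle missing data from participants who prematurely leave the study". It offers this as a protection against selection bias. It names no exception by outcome or by reason for leaving.
- The same paragraph covers behavioural scores, maternal outcomes and gestational weight gain, and states that "birth weight and length, BMI, and blood pressure will be compared using chi-square tests for proportions", with t tests and Mann-Whitney tests for continuous variables.
- **Type of Analysis** says that participants are "analyzed based on the group to which they were initially assigned, irrespective of the intervention they received using the intention-to-treat approach".
- **Results** identifies the early leavers so far: "Of the 300 recruited participants, 22.0% (n=66) were lost to follow-up due to miscarriage, change of hospital, refusal by family to continue", or migration within the country. It adds: "Of these 66 participants, 64% (n=42) belonged to the intervention group". It gives no count per reason.
- **Expected Secondary Outcomes** and the study timeline (Table 3) do not list miscarriage in the current pregnancy as an outcome. A previous miscarriage appears only as a possible confounder.

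**The concern.** Two kinds of absent value are placed under one rule.

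A woman who changes hospital or moves away still has a diet, a weight gain and, in time, a birth. Those values exist but were not observed, and imputation is a reasonable tool. After a miscarriage there is no later pregnancy diet, no birth weight and no infant blood pressure at one year. No imputation model can give such values a meaning. If they were filled in, the newborn and infant comparisons would describe a population that does not exist. Pregnancy loss, a known and important result, would be recorded only as attrition. Enrolment is in the first trimester, so some pregnancy loss was foreseeable.

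The second issue concerns the women whose data really are missing. Loss falls more heavily on the intervention arm. The Limitations section says that blinding was not possible and that behaviours are assessed subjectively. If leavers in one arm differ from stayers in ways the recorded data do not capture, standard imputation carries that bias into the result without showing it.

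**Working it through.** **1. Reproduce the article's figures.** 66/300 = 22.0% and 42/66 = 63.6%, stated as 64%. Both agree.

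**2. Arm sizes.** The readable text does not give them. The design has "two groups (ie, intervention and control) having an allocation ratio of 1:1" and randomisation in blocks of 6. 300/6 = 50 complete blocks, so 50 × 3 = 150 per arm. This is inferred.

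**3. Loss by arm.** Control losses are 66 − 42 = 24.
- Intervention: 42/150 = 28.0%
- Control: 24/150 = 16.0%
- Difference: 12.0 points
- Standard error: √(0.28 × 0.72/150 + 0.16 × 0.84/150) = 0.0473
- 95% CI: 12.0 ± 1.96 × 4.73 = 2.7 to 21.3 points
- Chi-square: each arm expects 33 lost and 117 retained, so 2 × 81/33 + 2 × 81/117 = 6.29, p = 0.012. With continuity correction p = 0.018; Fisher's exact test p = 0.017.

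If the intervention/control split were 145/155, the rates would be 29.0% vs 15.5%; at 155/145, 27.1% vs 16.6%. The imbalance does not depend on an exact 150.

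**4. How many women have undefined outcomes.** The number of miscarriages is not given, in total or by arm. The only bound is the total loss: at most 66 so far (42 + 24).

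**5. How far the comparison can depend on the missing values.** Suppose that the true mean among leavers differs from the imputed mean by δ_I in the intervention arm and δ_C in control. The estimated arm difference is then off by 0.28 δ_I − 0.16 δ_C. Two illustrations, neither of them an estimate:
- The dietary risk score moves in steps of 1.5 per food group. With δ_I = 1.5 and δ_C = 0 the error is 0.28 × 1.5 = 0.42 points on the 0 to 18 scale.
- For a proportion, the extreme bounds (all leavers in one arm succeed and all in the other fail, and the reverse) span 28 + 16 = 44 points. The differences used for sample size are 30 points for diet and supplements and 20 for physical activity.

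Both treat all 66 as missing. Once miscarriages are classified separately, the fractions 0.28 and 0.16 become smaller.

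**The case against.** **The plan never says that births will be imputed after a miscarriage.** This is correct. The rule speaks of missing data, and one can argue that a value that cannot exist is not missing. The sentence also follows directly on the mixed model for the repeated behavioural scores, so its author may have had only those in mind. A reader might infer that the trial will invent birth weights for ended pregnancies, but the document does not support so firm a statement. What stands is narrower: the rule is unqualified, the article itself puts miscarriage among the losses, and even the repeated behavioural scores are undefined once a pregnancy has ended.

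**Unequal loss does not contradict multiple imputation.** This is also correct. The article names no missingness assumption. Standard imputation assumes missing at random given the variables in the model, and 28% vs 16% is compatible with that if arm is included. A reader might infer that the imbalance proves informative loss, or that miscarriage differed between arms. Neither follows: reasons are not split by arm, the refusals are described as the family's, and change of hospital or migration may have nothing to do with diet or activity.

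**Details belong in an analysis plan that is not shown.** This holds for the imputation model and for the detail of sensitivity analyses, so their absence is not the point. The scope of the rule, however, is stated here, and it is too broad for the losses that the same article describes.

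**The figures are interim.** They are: 170 of the 234 remaining women had completed all four follow-ups. The final split may differ. The Limitations section does acknowledge attrition bias, but attributes it to the number of visits and the length of the study, which does not address a difference between arms.

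**Conclusion.** The point holds in a limited form. Read with the Results section, the imputation rule covers women whose pregnancies ended, for whom the later outcomes are undefined. It should be narrowed before analysis. The number of women affected is unknown and is at most 66 at the time of reporting.

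Separately, interim loss is 28% vs 16%, a difference of 12.0 points (95% CI 2.7 to 21.3), assuming 150 per arm. Chance is an unlikely explanation. The imbalance does not show that imputation under missing at random is wrong. It shows that the comparison rests on that assumption, and that a single imputation analysis cannot show how much depends on it. The 0.42-point and 44-point figures only illustrate sensitivity and do not measure a bias.

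**What to change.** 1. Classify pregnancy loss separately from withdrawal, and report both by arm, with reasons, on all 300 randomised women.
2. State that no value is imputed after a pregnancy has ended. Analyse behaviours while the woman is pregnant, and newborn and infant outcomes among births, labelled as conditional on birth.
3. Limit imputation to continuing pregnancies, with arm and earlier scores in the model.
4. Add a delta-adjusted (tipping-point) sensitivity analysis in which the shift may differ by arm and by reason for leaving. Reason for leaving should enter through these shifts. It cannot serve as an ordinary predictor, because it exists only for women whose later values are all absent.

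Cost: revised wording and some extra analysis. The article already cites reasons for loss, so the information should be at hand, and analysis was still ahead when it was written. The real downside is that newborn and infant comparisons become conditional on birth. They are then not fully protected by randomisation, and should be read beside the arm comparison of pregnancy loss.
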